## **Oversight**

1. Direct supervision for this phase of the study will be by the Iranian PI, [name], a psychiatrist at TUMS. Site level research personnel will be thoroughly trained in good clinical practice, human subjects procedures, and the importance of being alert for and documenting adverse events, protocol deviations, and participant concerns. All of these will be immediately communicated to [name] and the US PI.

The US PI will be in regular contact with the Iranian investigators and staff. Presently the US and Iranian teams have joint calls every 1-2 weeks and frequent email exchanges during the week. Once data collection is underway there will be one call a week for monitoring processes and one every two weeks to discuss data quality. The US PI and co-investigator have made one trip to Tehran for planning this phase of the study and plan subsequent trips to a) check on the process of data collection during the baseline phase, and b) observe the GP training. These trips are always subject to changes in international relations; in 2017 the Iranian and US PIs had to meet in Dubai.

2. Recruitment and informed consent: As noted above, children/youth will be recruited when they come for GP visits with a parent or legal guardian. Parents/guardians will be asked for written consent and children/youth for assent or co-consent as age-appropriate. Although the age of majority in Iran is 18, Tehran University ethical guidelines call for co-consent for children/youth ages 8 and older. If there is a concern about literacy, research assistants, will be able to go over the consent verbally. The consent process will take place in a private area in the clinic where the patient is being seen. Details about the consent process as it relates to specific risks are discussed below.

GPs will be recruited by announcing, in the course of existing TUCCP activities, the availability of new child mental health training. Opportunities for discussion about the training itself and its

evaluation will occur at both group and individual meetings. GPs will be individually and confidentially asked to provide consent. GPs choosing not to participate in the study will be able to continue in the TUCCP as at present but none of their patients will be recruited.

3. Overall data security: Precautions against loss of or breach of collected study data will include making sure that no study data forms or files ever contain identifying information (except those kept temporarily for follow-up tracking) and that linkage files are protected and destroyed as soon as possible. If linkage files ever need to be transported they will move separately from data files. Identifiable data will never be stored on portable devices unless this is for the purpose of locking those devices in secure physical storage. Appropriate firewalls, encryption, and password protection will be used for network-connected devices used to store or manipulate study data.

Individually identifiable data will initially be accessible to research assistants and the study's central office personnel in Iran. If patients are not chosen for follow-up, their linkage data will be immediately destroyed. If they are chosen for follow-up, linkage data will be kept only as long as needed to complete follow-up and extraction of associated data from the TUCCP system. Only de-identified data sets will be used for analysis and no identifiable data will be sent to the US investigators. Access to data will be limited to those study personnel who need access for processing or analysis, and only after training in human subjects research and data safety procedures. Data sharing outside the study will be managed through mechanisms set out in the NIH document NOT-MH-14-015 (including the use of appropriate language describing data sharing in the consent process).

4. Privacy for children/youth and parents: The consent process will make it clear that the parent and child/youth are free to discuss the SDQ, GHQ, and other forms with the GP. Regardless, any concern for serious mental health problems with possible harm to self or others will be reported to the GP (including positive parent responses for the self-harm item on the GHQ). This will be clearly stated in the consent.

Our GP training will address sensitivity to parent privacy in the context of integrating child/youth and parent mental health care. In most cases the parents will have a pre-existing, separate clinical relationship with the GP which should provide an avenue for a confidential discussion. Research assistants administering the GHQ to parents, should they feel the need to notify the GP of thoughts about self-harm, will be instructed to never do so in the presence of the child. Parents will be told about such possible disclosures as part of the consent process. However, unless there seems to be an emergency, the research assistants will consult with the parent (and with the Iranian PI if desired) to make the disclosure to the GP in a way that is maximally respectful of the parent's wishes and any additional clinical issues that might be relevant.

GP training will also cover the importance of asking about substance use and exposure to intimate partner violence, but this would take place as part of the clinical encounter and be at the GPs' discretion. GPs will be trained in the appropriate procedures to follow should a concern for child maltreatment arise during a visit. As noted above, *currently in Iran there is no legal obligation for GPs or study personnel to report suspected child maltreatment to authorities. Reporting obligations only apply to children who have been hospitalized.* TUCCP consultants are capable of helping GPs review options for responding to concerns about maltreatment and other forms of family violence.

To manage risk of disclosure during follow-up, research assistants will use only means of contact provided by parents and youth at the time of enrollment. When making follow-up calls,

research assistants will identify themselves only as calling on behalf of the GP until they are certain that they are speaking to the enrolled parent and that he or she is able to speak in confidence. Participants will have the right to leave the study at any point including declining to participate in follow-up.

5. Privacy for GPs: All provider data will be treated as confidential and managed in the same manner as patient data. In written accounts of the data for publication or internal reports care will be taken to sufficiently disguise quotes or results that could because of “small cell” issues lead to the inadvertent identification of a participant. Measures taken will include careful editing of data to remove names of individuals and practices, altering exact ages, not naming precise neighborhoods, and when necessary creating composite descriptions or paraphrases of accounts.

6. Coercion and involuntary participation by children/youth and parents: Children/youth and parents will not be able to chose whether or not their GP is participating in the study, but the consent process will disclose that the GP is participating in a trial of training whose purpose is to enable the GP to treat some mental health problems him or herself in collaboration with the CMHC. Our planned consent process is consistent with the Ottawa Statement on the Ethical Design and Conduct of Clinical Trials (Taljaard 2013). First, our initial stakeholder consultation process, while not designed to seek community consent, has served to identify needed changes to the study protocol (such as having parents as our informants even for youth 11-15). Second, though it is not possible to seek prior consent from GPs’ patients prior to GPs receiving child mental health training, for the duration of our study we will be seeking consent from patients coming to see trained GPs. The consent process will make it clear that patients may choose to request an immediate referral to the CMHC or any other mental health resource if they prefer that to following the GP’s advice for treatment (which may or may not include referral). This would be the equivalent of care as it is presently being provided. For this reason and because of the vulnerabilities discussed above we will make sure that consent processes are private and unhurried, with ample time for questions and decision-making and clear explanation of the option to not participate or to withdraw at a later point.

GPs cannot be blinded to which patients are participating in the study since patients may chose to ask questions prompted by administration of the baseline instruments (SDQ, GHQ, etc.). However, patient participation in the study involves only activities related to evaluation – consent or lack of it does not necessarily represent a preference for one form of treatment or another.

7. Coercion and involuntary participation by GPs: Consent forms will emphasize the voluntary nature of participation and that neither ongoing participation in TUCCP nor ongoing employment are in any way contingent on participation in the study.

8. Risk of inferior treatment of child/youth or parent mental health problems: The study design attempts to balance response burden and possible benefit by encouraging parents and children/youth to discuss with their doctor any concerns raised by completing the SDQ and GHQ. Intervention GPs will be supported in their use of treatments which are drawn from the evidence-based literature and that have been judged to be acceptable in the Iranian context through stakeholder consultation during the study’s developmental phase. In addition, there are several mechanisms that should minimize the risk of inferior treatment:

- Throughout the study both control and intervention GPs will continue to be members of the TUCCP and have ready access to mental health consultation and referral for both

- adults and children/youth. GPs will be free to refer any child for further evaluation or treatment at a CMHC regardless of study group assignment.
- In the Iranian system, while families can not directly access the CMHC without a GP referral, there are other mental health resources that they can access directly. However, there may be differences in cost depending on the family's insurance – referral to the CMHC by a GP as part of the TUCCP results in free treatment while self-referral elsewhere may be subject to fees of varying sizes. The consent process will remind parents and youth of these issues and that they may request a CMHC referral from their GP at any time.
  - As noted in the background section, the TUCCP involves regular monitoring of patient status by CMHC personnel who review records and discuss care of all patients registered with the system whether they are referred or cared for by the GP. This review is required before GPs can receive top-up payments for follow-up care. Thus, payment will be denied for follow-up care judged to be inappropriate.
  - Receptionists, who provide case management, constitute a second set of “eyes” interacting with families and assessing progress. Receptionists can trigger either return visits to the GP or a request to the GP to initiate a referral.
  - The study will have its own data safety management processes (see below).

**9. Increased work for GPs:** GPs will always have the option to refer patients to the CMHC if they find that their practice does not have the time to manage newly detected child/youth or adult mental health problems. There may also be offsetting benefits of taking on mental health treatment: there could be a reduction in return visits for somatic presentations of undetected underlying mental health problems, and there may be reductions in the frequency of visits with unanticipated psychosocial problems that disrupt a practice's ability to keep to its schedule of appointments. In addition, practices will receive top-up payments for patients they are able to successfully follow and manage.

**10: DSMP:** As noted above, the TUCCP has safety and quality of care monitoring built into its standard operating procedures; it also includes incentives for participating providers to adequately follow-up treated patients. However, the study will have its own data monitoring plan operating in parallel. The US and Iranian PIs will be primarily responsible for this second plan. Incoming data will be cleaned and compiled on a regular basis and examined for unusual or unexpected patterns. The PIs will be assisted in this task by a four-person DSMB that includes both Iranian and US members. The present version of the protocol reflects feedback from the DSMB. The DSMB will have internet meetings before study initiation, during the study roll-out, and at its conclusion.

Site level research personnel will be thoroughly trained in good clinical practice, human subjects procedures, and the importance of being alert for and documenting adverse events, protocol deviations, and participant concerns. All of these will be immediately communicated to the in-country director and the PIs. Lists of possible expected and unexpected adverse events will be developed during the initial stakeholder phase of the study and incorporated into training for research assistants in Iran and the US.

### **Benefits**

Patient participants may benefit by becoming more aware that their GP and/or her/his connections to mental health services are available for discussion and treatment of child and adult mental health concerns. Clinician participants may receive feedback or instruction as part of the study that will be of interest to them and that could add to their skill level.

The general public may benefit if the study's interventions prove to be practical and effective, since children's mental health services are currently difficult to obtain in Iran as in many other middle-income countries. These benefits seem reasonable in comparison to the relatively small risk of involuntary disclosure of information.

### **Payment and remuneration**

As noted above, GPs will receive about \$200 for participation in the two-day child mental health or control booster training and the trial. Families will receive a payment of about \$2 to compensate them for any extra time required at their index visit when they provide consent and baseline data.

### **Costs**

There are no direct costs associated with participation by patients. Patients asked to return to the GP for mental health treatment might have to pay for the GP visit whereas their treatment, had they been referred to the CMHC, would be provided without a charge. However, patients are likely to live closer to the GP office than to the CHMC meaning that they would not have to expend the cost of travel and the considerable time it could take to get to the CMHC, so costs are likely to be equivalent.

There are no costs to GPs for participation in the child mental health training, but there could be opportunity costs for participating if GPs were to be forgoing clinical income to attend.

I

### Data management

Incoming data from GP and patient instruments will be logged, examined for completeness, nonsense, and ambiguous entries. Queries will be sent to the research assistants to examine possibilities for re-contacting participants. Research assistants will use a messaging application to report on their daily progress with recruiting or follow-up and to be able to clarify or report any study issues immediately. Data collected on paper will be double entered. For each research assistant, a 5% sample of the participant forms that they collect will be checked by having a different member of the study team call the participant to verify key items. Supervisors of research assistants will make random visits to GP offices while research assistants are present to check on recruitment and data collection processes.

A trial data center in Tehran will be responsible for a) scoring baseline SDQ forms to determine which children/youth are eligible for the trial; b) maintaining files that link GPs to intervention status and children/youth to follow-up contact information; c) merging data collected directly from GPs and patients with data extracted from the TUCCP data system, and d) creating and maintaining unlinked merged data files. Duplicate merged unlinked files will be sent to the US study site for analyses, distribution to the Data Safety and Monitoring Board, and archiving. A final data set will be generated and deposited with the National Database for Clinical Trials Related to Mental Illness.

### Data analysis approach

Analysis will follow a pre-determined plan and take place under the direction of the trial statistician. Analyses will be masked to study arm until data collection is finalized. Exploratory analyses will confirm expected distributions and the prevalence and patterns of missing data.

We will use appropriate methods for missing or censored data, such as multiple imputation or full information maximum likelihood [59].

The outcomes in each set of analyses will first be explored with simple bivariate statistics. Multilevel models with random effects will model patient outcomes, which are clustered within GPs [60]. The basic approach has the following form: if the study ultimately has  $I$  clusters ( $i=1:I$ ), 3 time points ( $j=1:3$ ), and  $N$  patients per cluster ( $k=1:N$ ), individual patient outcomes are modeled as  $Y_{ijk} = \mu_{ij} + \gamma C_{ijk} + e_{ijk}$  where  $e_{ijk}$  has a  $iid N(0, \sigma_e^2)$  distribution. Individual covariates included at this level (denoted by  $C$ ) will include child age, gender, and initial SDQ symptom and functioning scores. The mean outcome for cluster  $i$  at time  $j$  can be expressed as:  $\mu_{ij} = \mu + \alpha_i + \beta Z_{ij} + X_{ij}\theta$ , where  $\alpha_i$  is a random effect for the cluster and  $Z_{ij}$  are the cluster-level covariates (e.g., public or private GP practice, practice size, the three staggered training waves to which the GP belongs), and  $X_{ij} = 0$  if the cluster is a control practice or  $= 1$  if it is an intervention practice.

Interaction terms between intervention status and a hypothesized cluster-level moderator (e.g. GP's public or private practice, practice size, training wave) will be used for exploratory analyses of effect heterogeneity.

Analysis will be by intent-to-treat based on the intervention status of the GP. However, intent-to-treat analysis does not take into account the level of intervention actually received by individual patients. Therefore, the intent-to-treat data will be presented along with data describing, for each arm: 1) the proportion of patients receiving any form of collaborative mental health treatment, 2) the proportion of patients who do receive mental health treatment who receive it solely from a CMHC; and 3) the proportion of patients whose GP left the collaborative during the course of the study. Only (3) will be considered a protocol deviation, since per the

986 protocol, GPs may opt to treat or refer any patient. In addition, the impact of implementation  
987 outcomes such as GP changes in attitude and confidence (“post-treatment mediator” variables)  
988 will be examined using causal mediation methods [61].

989

990

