## Population and recruiting:

**1. Children/youth and their parents:** The main participants in the trial are children/youth 5-15 years of age (male and female) and one of their parents or guardians (whoever accompanies the child/youth to their GP visit). These children will generally be coming to the GP for a non-emergent medical, emotional, or behavioral concern. Some children may have a chronic medical or mental health condition, but we will not recruit any child/youth who reports being in pain or who appears to be acutely ill. Children/youth who are actively being treated at the CMHC at the time of recruiting will also not be eligible. We plan to recruit approximately 1500 children/youth and 1500 parents (screening step) and follow about 350 of each (children who are SDQ+ and their parent) by telephone at 3 months and 6 months after the index visit.

The required patient sample size was estimated in four stages. We first used the "change" option in the "samps" routine in Stata Release 12 (StataCorp, College Station, TX 2011) to obtain a sample size disregarding clustering among general practitioners. The "change" option computes a t test on the difference in change scores (outcome minus baseline) between the intervention and control groups. The variance is adjusted for correlations between the outcome measures and between the outcome and baseline measures. We estimated that the difference in change scores at the final assessment would be about 2.5 points on the SDQ total difficulties scale, based on data from a prior trial conducted in primary care in the US (Wissow 2011) and on data from the UK child and adolescent mental health care system (Wolpert 2015). An estimated standard deviation of 7.2 was also drawn from these sources (thus an estimated effect size of .34). Correlations between baseline and outcome measures and between outcome measures were estimated at .37 and .55, respectively, also based on prior data from the US (Wissow 2011). With alpha=0.05 and power of 0.8 these parameters yielded a sample size of 135 per study arm (270 total).

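### The written model makes a child's repeated SDQ scores independent within a practice, contradicting the protocol's own .37 and .55 correlations; a 6-month contrast and likelihood handling of dropout suffer, the pooled arm term's standard error does not

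*Protocol*

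**What the plan says.** The Protocol's Data analysis approach section states that "Multilevel models with random effects will model patient outcomes, which are clustered within GPs". It then writes the model out for three time points. The practice term "is a random effect for the cluster and" is the only random effect, and the residual for each practice, time and child "has a $iid N(0, \sigma_e^2)$ distribution". The child-level covariates "will include child age, gender, and initial SDQ symptom and functioning scores". The arm enters as one indicator with one coefficient, constant over time; there is no arm-by-visit term. For missing data the section promises appropriate methods, "such as multiple imputation or full information maximum likelihood".

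The sample-size text under Population and recruiting, item 1, says: "Correlations between baseline and outcome measures and between outcome measures were estimated at .37 and .55, respectively". The same paragraph describes the 2.5-point difference in change scores as the one expected at the last assessment.

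**The concern.** Two parts of the protocol disagree. The sample size treats scores on the same child as clearly correlated. The analysis equation treats them as unrelated once practice and covariates are accounted for. This is a stated error structure, not a detail left open.

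Two things could follow. First, an unmodelled child effect has to go somewhere: part moves into the practice variance and the rest stays in the residual, so SEs and the practice ICC may be wrong. Second, likelihood-based handling of dropout works by borrowing from a child's observed scores through the modelled correlation. With no such correlation, a child's 3-month score says almost nothing about that child's missing 6-month score.

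**Working it through.** **Inputs (Protocol, Population and recruiting).** Difference 2.5; SD 7.2 (variance 51.84); correlations .37 (baseline-outcome) and .55 (outcome-outcome); 45 practices of 6 children; ICC .01; 20% loss. Half of 45 practices is 22.5 per arm.

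**1. The plan's own figure.** With one baseline and two follow-ups, the change-score variance factor is (1 + .55)/2 + 1 − 2(.37) = 1.035. Then n = 2 × (1.960 + 0.842)² × 51.84 × 1.035 / 2.5² = 134.8, so 135 per arm, as stated. Next, 270 × 1.05 = 283.5, taken as 284, and 284/0.8 = 355. The figure reproduces only with two correlated follow-up scores averaged. With the 6-month score alone the factor is 2 − 2(.37) = 1.26 and n is 165.

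**2. Correlation the model omits.** After baseline adjustment the two follow-up scores correlate at (.55 − .37²)/(1 − .37²) = .4131/.8631 = 0.48. The written model sets this to zero apart from the shared practice effect.

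**3. Variance components after baseline adjustment.** Total 51.84 × .8631 = 44.743. Practice a = .01 × 51.84 = 0.518. Covariance of a child's two follow-ups = .4786 × 44.743 = 21.415. Child c = 21.415 − 0.518 = 20.897. Residual e = 44.743 − 21.415 = 23.328.

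**4. Time-constant arm term.** The variance of a practice mean over 12 records is B = a + c/6 + e/12 = 0.518 + 3.483 + 1.944 = 5.945. The SE is √(2 × 5.945/22.5) = 0.727. With equal practices the written model estimates B directly, so its SE is also 0.727. Simulation agrees: model SE 0.709 against an empirical SD of 0.701 with two follow-ups as outcomes, and 0.473 against 0.474 with all three scores as outcomes.

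**5. Arm effect at 6 months (arm-by-visit term added).**
- Correct SE: √(2 × [0.518 + (20.897 + 23.328)/6]/22.5) = √(2 × 7.889/22.5) = 0.837.
- Written model, large-sample within-practice variance: W = [12(c + e) − (2c + e)]/11 = (530.70 − 65.12)/11 = 42.325.
- Written model, practice variance: A = B − W/12 = 5.945 − 3.527 = 2.418.
- Written model SE: √(2 × [2.418 + 42.325/6]/22.5) = √(2 × 9.472/22.5) = 0.918.
- Ratio 0.918/0.837 = 1.10.
- Apparent ICC: 2.418/(2.418 + 42.325) = .054, against the .01 assumed.

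Simulations with equal practices gave 0.905 against 0.822 (6 children per practice) and 0.885 against 0.832 (about 6.3 children, 6% too wide). In the latter, power was 80% against 83% with a child effect, and the estimated ICC was 0.048 against 0.016.

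**6. Dropout under likelihood estimation.** Assume 20% loss at 6 months, tied in one arm only to the 3-month score s (in SD units) with odds ratio 2 per SD: logit p = k + ln(2)·s, with k set to give 20% loss. The retained children's mean of s is −E[s·p]/(1 − .20) = −0.129 by numerical integration. The baseline-adjusted 6-month bias is 0.129 × 7.2 × (.55 − .37²) = 0.129 × 7.2 × .4131 = 0.38 points. In a term pooled over two follow-ups, weighted 1 and 0.8 for the records available, it is about 0.38 × 0.8/1.8 = 0.17. Simulation with odds ratio 2 gave 0.34 at 6 months. A steeper assumed dependence (log-odds slope 1 per SD) gave 0.47. With a child effect in the model the bias was about zero in both simulations. With the same dependence in both arms it is about 0 under no effect, and about 0.06 at a true difference of 2.5, even without a child effect.

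**The case against.** The best defence is that the written equation contains no 6-month effect. Its one arm coefficient is constant over time, and step 4 shows that its SE is right with near-equal practices. The sample-size arithmetic also matches an average over two follow-ups rather than the 6-month score alone. This stands, and it limits the SE point to a contrast the protocol suggests in words but does not write. Even there the error is conservative, and the simulated power stays at the planned 80%.

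Multiple imputation, the other example named, can use the 3-month score if the imputation model includes it. That also stands: the missing-data point applies to the likelihood route only.

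The section presents the equation as a basic form, and an analysis plan not seen here may refine it. That has less weight, because the residual assumption is stated outright and conflicts with the protocol's own correlations.

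A reader might infer more than the documents support:
- **False positives, or a wrong interval for the effect as written.** Neither follows from steps 4 and 5.
- **No earlier score is used.** Baseline SDQ is a covariate; only the 3-month score is lost.
- **Any dropout related to the 3-month score biases the comparison.** The dependence must differ by arm.
- **A misleading ICC will be published.** The protocol uses an ICC for sample size but does not promise to report one.
- **The SE is 14% or 20% too wide.** The first needs a cluster-size coefficient of variation of 0.6, which is not in the protocol. The second (1.198 against 1.001 in simulation) is for a change contrast fitted to all three scores, which the equation does not specify.

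**Conclusion.** The concern holds in limited form. The stated error structure contradicts the within-child correlations used to size the trial. For the single arm term this does no material harm to the SE when practices are near equal. For a 6-month arm-by-visit contrast the SE is about 6-10% too wide with equal practices under the protocol's figures, and the model's practice ICC is about .05 rather than .01.

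The more consequential part is dropout. Full information maximum likelihood under this model gives almost no protection when loss depends on the 3-month score differently by arm. The size, about 0.3-0.5 points at 6 months and about 0.2 in the pooled term against a planned difference of 2.5, rests on an assumed mechanism: 20% loss, one arm only, at the odds ratios shown. Nothing in the protocol predicts that pattern, and the bias is near zero if the dependence is the same in both arms.

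**What to change.** - Replace the independent-residual statement with a child random intercept nested in the practice effect, or with an unstructured residual covariance across a child's visits.
- If the 6-month effect is the target, add visit and arm-by-visit terms and name that contrast.
- If multiple imputation is used instead of likelihood estimation, state that the imputation model includes the 3-month score.
- If a practice ICC is reported, take it from the model with the within-child correlation.

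The cost is a few lines in the model statement. No new data are needed and the sample size does not change.
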